
#### Assessing physical activity every 2 weeks

Quantifying physical activity will be critical for indicating the level of adherence to the intervention and to assess whether the participants have moved towards adopting a more physically active lifestyle [86]. In addition to obtaining estimates of physical activity using accelerometry, a standardized questionnaire will be administered by a trained researcher in-person/face-to-face in the supervised canoeing group, and via telephone in the unsupervised group every 2 weeks. The periodic assessment and contact with the participants are also a key strategy to promote retention, especially in the home-based group. The questionnaire will be modified from the Brazilian version [87] of the Minnesota Questionnaire on Physical Activities, Sports and Leisure [88], which surveys time spent on various activities, both domestic and sports. This physical activity questionnaire will be used to measure 1) the time participants spent doing accumulated physical activities, including lifestyle physical activity and incidental movement, referred as “Unscheduled Movement”; 2) the time spent in physical activities specifically scheduled to meet the goal of 150 min of physical exercise per week; 3) and the total time spent sitting, whether in leisure activities (such as watching television and cell phones) or in work activities. Self-reported measures of physical activity and sedentary behavior have been criticized for low validity and reliability. As a result, caution is advised when relying on questionnaires to assess physical activity and sedentary behavior [89]. To address this issue, physical activity will also be assessed by accelerometer pre-intervention, at 8 weeks and post-intervention (16 weeks), aiming to provide a more objective estimate to compare and validate the follow-up physical activity and the sedentary behavior questionnaire.

#### Physical activity level

Time, intensity, and frequency of physical activity engagement will be assessed using ActiGraph GT9X accelerometers (ActiGraph Pensacola, USA) at pre-intervention (with aims to provide baseline comparisons), during the intervention (mid-way, approximately 8 weeks of intervention), and post-intervention (after 16 weeks). The ActiGraph GT9X is a small, light-weight accelerometer (19 g; 4.6 cm × 3.3 cm × 1.5 cm) capable of recording accelerations in the vertical (Y), horizontal right-left (X), and horizontal front-back (Z) axes to compute vector magnitude [VM = √(axisY^2^ + axisX^2^ + axisZ^2^)]. The ActiGraph GT9X records accelerations over pre-defined time periods (“epochs”). Following which, Actilife software (ActiGraph Pensacola, USA) is used to convert raw acceleration data into “activity counts” for analysis. In this study, the GT9X+ will be initialized to record accelerations in 60-s epochs over a period of 7 days at each assessment time point. During this 7 days, participants will be asked to wear the GT9X attached to an adjustable elastic belt on their right hip in a vertical position [90, 91], and to remove the device only for sleeping and water-based activities (e.g., swimming, bathing).

##### Data reduction

Following 7 days wear*,* data will be downloaded using Actilife and cleaned to check for periods of non-wear. Non-wear criteria will be ≥ 60 min of consecutive “0” counts, with a spike tolerance of 2 min [91]. For accelerometer data to be considered valid and retained for use in subsequent analysis, participants will be required to have worn the accelerometer for ≥ 10 h/day, on ≥ 4 weekdays, including ≥ 1 weekend day [91]. Sedentary time as well as time, frequency, and intensity of PA will be estimated by applying count-based vector magnitude (VM) cut-points to valid accelerometer data. Cut-points that will be applied were selected based on widespread use in epidemiological research using the ActiGraph [91] and are considered in counts/min as sedentary time = < 100, light-intensity PA = 101–2019, moderate-to-vigorous intensity PA = ≥ 2020. The average daily time spent sedentary, in light and moderate-to-vigorous intensity (min/day), as well as the average daily proportion of time spent in these behaviors (i.e., % wear time = behavior [min/day]/total GT9X+ wear time [min/day]) × 100) will be computed for analysis.

#### Physical functioning tests

Participants will undertake a circuit of six functional fitness tests, designed to systematically address parameters associated with independent functioning: aerobic endurance, upper and lower body strength and flexibility, and agility/dynamic balance.
i.*Aerobic endurance*: Two-minute step test will be used to assess gait functionality. This test correlates highly with peak oxygen consumption, the primary outcome of this study [92].ii.*Upper body muscular strength*: (i) Maximal isometric handgrip test (Jamar®) will evaluate hand muscle strength during the handgrip test, three alternating attempts will be made for each arm and the highest score will be used for analysis [62]; (ii) Arm curl test will be used to assess arm muscle strength. Participants will do forearm flexions during 30 s with a 2-kg weight. Three alternating attempts will be made for each arm, the first attempt will be considered a familiarization, and the mean of the last two curls will be used for analysis [92].iii.*Lower body muscular strength*: Chair stand test will be used to determine lower limb strength. This test comprises sitting and standing repeatedly without the aid of the arms, for 30 s. Participants will attempt the test once and their score will be used for analysis [62].iv.*Upper body flexibility*: Back scratch test will be used to measure general shoulder range of motion (flexion and extension) in the standing position. Three alternating attempts will be made for each arm. The first attempt will be considered a familiarization and the average of the last two attempts will be used for analysis [92].v.*Lower body flexibility*: Sit and reach lumbar flexibility test will evaluate lower body range of motion using sit and reach bench. Three attempts will be executed. The first attempt will be considered a familiarization and the average of the last two attempts will be used for analysis [93].vi.*Agility/dynamic balance*: Timed up-and-go test will be used to assess functional mobility as the time needed for the participant to get up from a chair, walk 3 m, and return to the original position—Two attempts will be made and the shortest time between them will be used for analysis [94].

### Statistical analysis

#### Power calculation and sample size

Sample size calculations were performed based on the predicted maximum oxygen consumption (VO_2_—ml/kg min) of patients with breast cancer [95] using G-Power Software (Version 3.1.9.2). Sample size was carried out a priori, assuming a power (1 − *β* error) of .90 and assuming *α* error of .05. The calculation was based on an F test with analysis of variance by repeated measures and between- and within-group effects. To eliminate possible sample size bias, the Hedges *g* calculation was used. The effect size used in the calculation was based on the work of Courneya et al. [95] considering the maximum oxygen consumption (VO_2_—ml/kg min) of patients with breast cancer. A pre- to post-test correlation value of 0.50 was assumed. Power calculations indicated a sample size of *n* = 15 participants per group were required to achieve a power = .90 and *α* error = .05. To account for participant drop-out during the intervention, the sample size was increased by 20% to *n* = 18 participants per group. Therefore, we aim to recruit a total sample of *n* = 36 participants to the study.

#### Data analysis

The data analyst will receive the raw data coded for participant names and group allocation after completion of data collection. Group allocation will be unblinded after termination of data analyses. The Shapiro–Wilk and Levene’s tests will be used to determine normality and variance equality, respectively, and non-normal scale data will be log transformed. If the transformation does not produce a normal distribution, residual analyses will be performed to test if influential points change the interpretation of the results. If interpretations change, these points will be manually removed. Linear mixed models having group and time as fixed factors and participants as a random factor will be performed for each dependent variable [maximal aerobic capacity (VO_2_ max), daily physical activity, and adherence to physical activity guidelines (assessed via accelerometry and questionnaire), physical functioning (assessed via muscle strength, balance, and agility), self-reported quality of life, fatigue and perceptions of self-image (assessed via specific validated questionnaires), presence of lymphedema, and body composition and immune function]. Baseline differences in outcomes will be examined by independent *t*-test. An analysis of covariance (ANCOVA) will be implemented including the baseline variable as a covariate, group as a fixed factor, and participants as a random factor, in case of differences in baseline values between groups. An intention-to-treat analysis will also be performed in case of a high incidence of missing values, using linear mixed models; the first analysis will be performed removing the missing values, while the second analysis will be performed incorporating the missing data points to determine the impact of missing values in the overall results [96]. Whenever a significant F-value is obtained, a post hoc test with Tukey’s adjustment will be performed. Ordinal data will also be analyzed using mixed models having group and time as fixed factors, and participants as random factor. Nominal data will be compared using chi-square distributions and significance will be determined by residual analyses (< − 2 or > 2).

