**Fig. 2 Fig2:**
[figure not shown]
Overall schedule of enrollment, intervention, and assessments following the Standard Protocol Items: Recommendations for Interventional Trials (SPIRIT)

Participants who meet the eligibility criteria and have been authorized for participation will receive a detailed explanation about the protocol and provide written consent, including storage of biological specimens. Participants will be informed that they can withdraw from the study at any time without consequence. The intervention will be discontinued for the participants who 1) request to stop, 2) have any surgery scheduled, or 3) suffer any injuries that prevent the practice of physical activity or exercise. The reasons for drop-out will be recorded and all data collected from these participants will be included in the analysis. From the time point of discontinuation, no outcome will be collected from those participants. The protocol poses a low risk to the participants regarding blood sampling and cardiorespiratory evaluation. Both procedures will be performed by an experienced physician ([name]) and participants will be monitored after the cardiorespiratory fitness test until they fully recover from the exercise bout. During the canoeing or exercise training sessions, participants will always wear life jackets, and if they feel any discomfort, they will receive local medical care and will be taken to the nearby University Hospital if needed. Likewise, all participants will continue their routine medical care at ICESP.

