i.European Organization for Research and Treatment for Cancer Quality of Life Questionnaire - Core 30 (EORTC QLQ-C30) will be used to assess a broader dimension of quality of life in cancer survivors [76]. This validated instrument is composed of three scales that examine global health, functional aspects and patient’s symptoms. It comprises 28 questions about difficulties of daily life and symptoms with scales from 1 (no difficulty/distress/symptom) to 4 (a lot of difficulty/distress/symptom), and two questions about general health and quality of life with scales from 1 (terrible quality) to 7 (great quality). The Brazilian version has been previously validated among people living with cancer [77].ii.36-Item Short-Form Health Survey (SF-36) will be used to evaluate health status [78]. It comprises eleven questions (five of which are multi-item) that evaluate health status including physical and social functioning, physical and emotional role, mental health, bodily pain, general health perceptions, and vitality. The Brazilian version of SF-36 was already applied to women with a history of breast cancer [79].iii.Piper Fatigue Scale-Revised (R-PFS) will be used as a subjective fatigue assessment method. Its psychometric properties have been validated in female survivors of breast cancer [80]. The Brazilian version contains 22 items on three dimensions (behavioral, affective, and sensorial–psychological) and provides an overall of fatigue score on a scale from 0 (the best status evaluation) to 10 (the worst status evaluation). This instrument has been validated for oncological use in Brazilian populations [81], particularly for breast cancer survivors [82].iv.Body Image Scale [83] will be used to assess body image. Its higher scores indicate greater body appreciation and it addresses six domains of body image: vulnerability, body stigma, limitations, body concerns, transparency, and arm concerns. The Brazilian version presents 44 statements for which the participant must decide how they apply to her, on a scale varying from 1 (Strongly disagree/Never/Almost Never) to 5 (Strongly Agree/Always/Almost Always). It has also been demonstrated to be reliable and valid [84].v.Inventory of Motivation to the Regular Practice of Physical Activity (IMPRAF-54, Brazilian acronym) will be used to assess physical activity motivation. The short version of this form contains 54 items for which the participant must decide how they reflect her motivation to engage on physical activity, using a scale varying from 1 (this motivates me very little) to 5 (this motivates me a lot). All affirmations start with “I engage in physical activity to...” followed by sentences that reflect six dimensions (nine items for each), such as control of stress (e.g., decrease irritation), health (e.g., acquire health), sociability (e.g., meet friends), competitiveness (e.g., be champion in sport), esthetic (e.g., accomplish a beautiful body), and pleasure (e.g., achieve my ideals) [85]. The raw score obtained in each dimension will be related to a percentile according to participant’s gender and age, which will provide the participants’ motivational profile.

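### Influential points are removed when removal changes the conclusion, so for any outcome reaching that step the trimmed-data conclusion always replaces a differing all-data one

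*Protocol article*

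**What the plan says.** The Data analysis section sets out a sequence. Normality is tested by Shapiro-Wilk, and "non-normal scale data will be log transformed". If that does not produce normality, residual analyses ask whether influential points alter the interpretation of the results. The last step reads: "If interpretations change, these points will be manually removed".

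The sequence stands ahead of the linear mixed models, which are to be fitted for every dependent variable, aerobic capacity (the primary outcome) included. The section does not define an influential point, does not require evidence of a measurement or entry error, and does not say that the all-data result stays primary or that both results are reported.

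The same section says the analyst works with coded groups until the analyses are finished. The Data management section separately provides range, valid-value and consistency checks.

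**The concern.** An influence check is normally a sensitivity analysis: it tells the reader how far a result depends on a few observations. Here it replaces the result. Points are removed because they matter to the answer, after the answer has been seen with and without them. Values that have passed the data checks can therefore be discarded with no finding that they are wrong.

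At stake is the stated error rate, for the primary outcome as much as for the secondary ones. Removing extremes shrinks the residual variance, while the test treats the remaining sample as if it were complete. In a trial of 36 women, one or two observations can decide whether a comparison reaches significance.

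**Working it through.** **1. What the rule does by construction.** Let A be the all-data conclusion and T the conclusion without the influential points.
- If A = T, nothing is removed, and the reported conclusion is T.
- If A ≠ T, the points are removed, and the reported conclusion is T.

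Once the step is reached, the reported conclusion is always T. This needs no assumption about distributions or cut-offs.

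**2. Inputs from the plan.** The sample size section gives "to achieve a power = .90 and *α* error = .05", a pre-post correlation of 0.50, and 15 per group raised by 20%: 15 × 1.2 = 18, as stated. The 15 itself can be checked only backwards, because no effect size is printed. For a group-by-time F test with N = 30, m = 2 times and ρ = 0.5, the noncentrality is λ = f²·N·m/(1 − ρ), and 90% power needs f ≈ 0.307, so λ = 0.307² × 30 × 2/0.5 ≈ 11.3. The figure is attainable but cannot be confirmed. This does not affect what follows, because type I error is computed with no group effect.

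**3. Assumptions needed to size the effect.**
- Test: two-sample t-test on change scores, which equals the group-by-time test with two time points and complete data.
- Gate: Shapiro-Wilk p < 0.05 on residuals, with the log step assumed not to help.
- Influential: Cook's D > 4/n. With two groups of 15, leverage is h = 1/15 and D = (r²/2) × h/(1 − h) = r²/28. D > 4/30 = 0.133 therefore means |r| > √(28 × 0.133) ≈ 1.93, where r is the studentised residual.
- Changed interpretation: the p < 0.05 decision changes. Only then are the points removed.

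**4. Results, 15 per arm, no group effect, nominal 5%.**

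| Distribution of changes | Overall type I error under the rule |
|---|---|
| Normal | about 5.3% |
| t, 5 df | about 6.0% |
| t, 3 df | about 6.6% |

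Among data sets that reach the step, the error is about 7% to 15%, against about 3% to 6% in the same data sets with all points kept. Changes towards significance outnumber changes away from it by 140 to 27 (t5) and 184 to 33 (t3).

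**5. Arithmetic check on one cell.** In a separate set of 8,000 trials (t3, 15 per arm, same cut-off), 42.3% reached the step. There, 202 results became significant and 41 lost significance.
- Overall: 4.42% + (202 − 41)/8,000 = 4.42% + 2.01% ≈ 6.4%.
- Within the step: 0.423 × 8,000 = 3,384 data sets, and 3.22% + 161/3,384 = 3.22% + 4.76% = 7.98%.

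The Monte Carlo standard error of an overall rate at 8,000 trials is about √(0.05 × 0.95/8,000) = 0.24 points, so the overall rate for normal data cannot be told apart from 5%.

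**6. Sensitivity to the undefined cut-off.** The runs covered normal, t5 and t3 changes at 15 and 18 per arm, plus a 10% contaminated normal at 15 for the residual cut-offs.
- Cook's D > 4/n or studentised residuals beyond 2, 2.5 or 3: 4.8% to 7.1% overall and 5.9% to 17.5% within the step (2.9% to 6.5% with all points kept).
- Influential meaning any single point whose removal reverses the decision: 5.2% to 7.7% overall and 10.1% to 13.4% within the step.

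**The case against.** The strongest reply is that removal sits behind three conditions: the data are non-normal, the log transform fails, and the interpretation changes. Near-normal outcomes rarely get there, and in simulated lognormal data with the log step applied only 3.5% of trials reached deletion. This stands, and it limits the size of the problem. It does not repair the rule for outcomes that do get there.

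Coded groups are a partial answer. They limit steering towards a named arm, but the trigger itself requires the analyst to see whether the coded comparison changes. The wording is also symmetric and can remove significance as well as create it, but the simulated changes were not symmetric.

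Several stronger readings are tempting and not supported:
- *The error rate is 7% to 11% for every outcome.* Those rates arise only if influential points are trimmed in every trial, ignoring the conditions above.
- *One or two women are lost per outcome.* About 1.5 to 1.9 of 30 points are flagged at this cut-off, but the rule removes them only when the decision changes, which averages about 0.01 to 0.05 removals per outcome.
- *The estimated difference is biased.* In gated null runs the mean between-arm difference lay between −0.011 and 0.004, within about two standard errors of zero. Error inflation is shown; directional bias is not.
- *The log step drops the women with least fatigue.* The fatigue score does run "on a scale from 0 (the best status evaluation) to 10", and the log of zero is undefined. But the plan does not say that zeros are dropped or that this score must be logged, and ordinal data have their own sentence. An offset is a detail an article may leave out.
- *The rule contradicts the promise that* "all data collected from these participants will be included in the analysis". That promise concerns women who discontinue the intervention, not outlying values.

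**Conclusion.** The rule is wrong as written. That the trimmed conclusion always prevails once the step is reached follows from the text alone. This is a stated rule rather than a missing detail, so a separate analysis plan could repair it only by contradicting it.

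The size is moderate and concentrated. Overall type I error rises by roughly 0 to 2 points above 5% for the distributions examined with Cook's D. Where the step is reached, it is about double to triple that of the all-data analysis in the same data sets. These figures rest on an assumed cut-off, an assumed normality gate and a log step taken not to help; the plan fixes none of them numerically. The primary outcome is not exempt, so the sentence should be changed before groups are unblinded.

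**What to change.** Replace the removal sentence with:

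> All verified values stay in the primary analysis; only confirmed measurement or entry errors are corrected or excluded, blind to arm and before analysis. An analysis without influential points is reported beside the primary result as a sensitivity analysis and never replaces it.

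The checks already planned under Data management can supply the verification. A permutation or bootstrap test for outcomes with doubtful distributions is optional. The cost is the wording of the analysis section, with no change to sample size, visits or data collection. The trial status section shows recruitment still open, so the change can be made and dated before analysis.

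### No stated test is tied to the hypothesised difference in change: the group-by-time term is not named, the baseline-adjusted model is conditional, and any significant F opens Tukey comparisons

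*Protocol article*

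**What the plan says.** The protocol article describes a superiority trial (Study design) whose hypothesis is that the supervised arm improves more than the unsupervised arm. Assessments are made before the intervention and at 16 weeks, with physical activity also measured at 8 weeks (Assessments).

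The Data analysis section sets the model for scale outcomes: "Linear mixed models having group and time as fixed factors and participants as a random factor will be performed for each dependent variable". It repeats the two factors for ordinal outcomes: "Ordinal data will also be analyzed using mixed models having group and time as fixed factors, and participants as random factor". The follow-up rule is: "Whenever a significant F-value is obtained, a post hoc test with Tukey’s adjustment will be performed". A baseline-adjusted model exists but is conditional. First, "Baseline differences in outcomes will be examined by independent *t*-test"; ANCOVA is then used "in case of differences in baseline values between groups".

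The sample size section says: "The calculation was based on an F test with analysis of variance by repeated measures and between- and within-group effects", "assuming a power (1 − *β* error) of .90 and assuming *α* error of .05". It assumes a pre-post correlation of 0.50 and arrives at 15 per group, raised by 20% to 18. No numerical effect size is given.

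**The concern.** With one measurement before treatment and one after, the treatment effect is the between-arm difference in change, or equivalently in aim the week-16 difference adjusted for baseline. The section names neither as the deciding test.

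The two factors that it does name answer other questions. The group factor compares arms averaged over both visits, and the first visit precedes treatment. The time factor asks whether women improve on average. That is likely in both arms, since both are advised to reach at least 150 minutes of exercise a week. Because the Tukey step follows any significant F, a time effect alone is enough to open it.

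At stake is whether the primary question has one decisive, adequately powered test, and whether post hoc comparisons could suggest a benefit of supervision when both arms gained equally.

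**Working it through.** **The plan's own figure.** The 15 per group cannot be reproduced, because the effect size is not stated. Using the noncentral F for 2 groups and 2 times at ρ = 0.5, a total of N = 30 results from either of two assumptions:
- within-between interaction, λ = f²·N·2/(1 − ρ): f about 0.308 to 0.318;
- between-group effect, λ = f²·N·2/(1 + ρ): f about 0.532 to 0.550.

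The text does not clearly say which was used. The inflation is 15 × 1.2 = 18, as stated.

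**Does the ANCOVA route apply to peak VO2?** Randomisation is 1:1 within quartiles of baseline peak VO2. In a simulation of 36 women with normal values, 9 per quartile split 5/4, the baseline t-test was significant in 0 of 20,000 trials. For the primary outcome the conditional ANCOVA would almost never run.

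**Reading (a): additive model, group + time.** Take n = 15 per arm, ρ = 0.5, SD = 1 at both visits, and d = difference in change.
- Interaction (for reference): variance of the contrast = 2(1 − ρ)·2/n = 0.133. Power 0.90 needs d = 1.23 SD (f = d/4 = 0.307): λ = 1.226²/0.133 = 11.28 on 1 and 28 df.
- Group F at that d: target d/2 = 0.613 SD, variance [(1 + ρ)/2]·2/n = 0.100, λ = 0.613²/0.100 = 3.76, power 0.465.
- ANCOVA fitted in all cases at that d: variance (1 − ρ²)·2/n = 0.100, λ = 1.226²/0.100 = 15.04 on 1 and 27 df, power about 0.96.

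With d reset at each correlation so that the interaction keeps 0.90, the group F has power 0.66 (ρ = 0.3), 0.28 (0.7), 0.19 (0.8) and 0.12 (0.9).

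**Reading (b): factorial model, with Tukey over the four arm-by-time cells.** Simulation with 15 per arm, ρ = 0.5, equal gains in both arms and no true difference. The Tukey critical t is 2.73 (4 cells, 28 df).

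| Assumed gain in both arms | Tukey: supervised arm only significant | Interaction F significant |
|---|---|---|
| 0.3 SD | about 6% | about 5% |
| 0.6 SD | about 22% | about 5% |
| 0.9 SD | about 16% to 17% | about 5% |

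At a 0.6 SD gain the time F, which opens the Tukey step, is significant in about 89% of trials. The gains are assumptions; the documents give none.

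**The case against.** The strongest reply is that naming group and time lists the factors of a factorial model and that the interaction is understood. The Tukey step supports this: with two groups and two times it adds nothing to a main effect, so for the pre/post outcomes it only makes sense if arm-by-time cells are estimated. The sample size wording may also refer to a within-between interaction. This stands as a fair reading, and it is why the consequence is split in two. It does not settle the point. The term is unwritten in both model statements, and the Tukey gate is tied to no term under either reading.

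Four stronger inferences are tempting and are not supported:
- **That the plan does not test the treatment effect at all.** Under randomisation the group F is a valid 5% test, though of a diluted quantity, and the conditional ANCOVA does test the effect when it is triggered.
- **That the power loss and the misleading post hoc pattern both apply.** An additive model fits the same change in both arms, so it cannot yield a supervised-only gain. A factorial model can, but it also tests the interaction. Only one of the two harms can hold.
- **That the trial has half its stated power.** This presumes that the interaction was powered. If the between-group F was powered, it has 0.90 by construction. That would imply a difference in visit averages of 2f, about 1.06 to 1.10 SD, and so a difference in change of about 2.1 to 2.2 SD.
- **That the investigators will claim superiority from within-arm changes.** The article's hypothesis and discussion speak of comparisons between arms. The plan leaves that route open but does not adopt it.

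The 22% figure is also near the worst case. With no common gain the supervised-only rate is about 0.5%. When allocation within quartiles is simulated, the 0.6 SD figure is about 19% and the interaction rejects in about 2.7%.

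**Conclusion.** The point holds as a specification gap that should be fixed. No test in the Data analysis section is tied to the hypothesised greater improvement. The one model that isolates the effect directly, the ANCOVA, depends on a baseline difference that the randomisation scheme all but rules out for peak VO2.

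If the model is additive, the between-arm test has about 0.47 power at a 1.23 SD difference in change. This is conditional on the interaction having been the powered term, on ρ = 0.5 and on equal variances. If the model is factorial, the interaction is tested properly, and the weakness is the open post hoc gate: about 6%, 22% and 16% to 17% supervised-only findings at assumed equal gains of 0.3, 0.6 and 0.9 SD. The documents do not show which reading is intended, so neither figure can be given as the size of the error.

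**What to change.** In Data analysis:
- State one primary contrast for peak VO2: the between-arm difference at week 16 adjusted for baseline in all cases (ANCOVA), or the group-by-time contrast, two-sided 5% with a 95% confidence interval. The ANCOVA is the better choice, with about 0.96 power at the effect that gives the interaction 0.90.
- Remove the baseline t-test as the trigger for adjustment.
- Say that superiority is claimed only from the primary contrast and that within-arm changes are descriptive.
- Tie any Tukey comparisons to that term instead of to any significant F.
- For accelerometry, measured at three times, name the between-arm difference at week 16.

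In the sample size section, say which term the 0.90 power refers to and give the effect size used.

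The cost is wording only: no new data, visits or participants. The article reports recruitment as still under way, so the change can be made before the allocation codes are broken.
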